## Abstract

**Background:**

Healthy behavior is an essential component in type 2 diabetes (T2D) management. Promoting healthy lifestyle is one of the priorities of primary health care in Oman. This study aims to evaluate the effectiveness of a multi-component intervention in promoting physical activity (PA) and healthy diet and its implications on body mass index and glycemic control in adults with diabetes attending primary care.

**Methods:**

A one year 1:1 cluster randomized controlled trial will be utilized to compare the use of phone consultations, a multi component interactive phone application and pedometers with the usual diabetes care on promoting PA and healthy diet. Participants will be screened for inactivity and should be T2D, aged18–65 years, and overweight or obese. Eight primary centers will be randomly selected in each arm (*n* = 375). The primary outcome is the between arms differences in PA and diet scores, BMI and HbA1c over 12 months from baseline. Additionally, secondary outcomes will include cardiovascular outcomes (BP, and lipids).

The trial has received ethical approval from the Omani Research and Ethical Review and Approval Committee. All eligible participants will be invited to their respected health centers to provide informed consent.

**Discussion:**

This study will contribute to the integration of healthy lifestyle approach using artificial intelligence to primary diabetes care. Results from this study will be disseminated through workshops, policy briefs, and peer-reviewed publications, local and international conferences.

**Trial registration:**

Trial registration number ISRCTN71889430. Date applied: 28/11/2020. Date assigned: 01/12/2020.

**Supplementary Information:**

The online version contains supplementary material available at 10.1186/s12889-021-11549-3.

## Background

In 2019, the International Diabetes Federation (IDF) estimated that more than 8% of the global population aged 20–79 have diabetes, of which 90% have type 2 diabetes (T2D). In countries of the Middle East and North Africa (MENA) region, it is estimated that the number of people with diabetes will increase by 96% by 2045, which will be the second-highest regional increase after Africa (143%). The negative impact of diabetes on health care system expenditures, population productivity and quality of life is of great concern.

In Oman, a national survey in 2017 reported non-communicable (NCD)-related risk factor prevalence as obesity 66%, high blood pressure 32.2%, cholesterol ≥5 mmol/L 37%, insufficient physical activity 42%, and unhealthy diet 56% [1]. The prevalence of diabetes had shown a dramatic increase from 8.3 to 11.6% to 12.3% in 1991, 2000, and 2008, respectively and recent estimates are in the order of 15%, exceeding the global rates [2, 3]. In addition to that, two-thirds of adults with diabetes are overweight or obese.

Physical inactivity is estimated to be the principal cause for 27% of diabetes, and 30% of ischemic heart disease [4]. Similarly, greater sitting time known as sedentary behavior (SB) is considered an independent risk factor for diabetes, cardiovascular disease, and all-cause mortality [5–8]. Sitting more than 8 h/day leads to increase risk of all-cause mortality even among those achieving the recommended 150 min/week of moderate to vigorous physical activity (PA) [9].

Overweight or obesity is the fifth leading risk factor for global death and the third in high income countries [10]. Around 3.4 million adults die each year as a result of being overweight or obese [11, 12]. Obesity has been attributed to the burden of 44% of diabetes, 23% of the ischemic heart disease and up to 41% of certain cancers [13].

The evidence for the impact of lifestyle modifications including diet, physical activity (PA), and reducing sitting time in controlling blood glucose levels and in the overall management of diabetes is well documented especially within clinical setting [14–16]. Increasing PA, together with reducing and regularly interrupting sitting time are now considered cornerstones of diabetes management [17]. However, a recent study in Oman showed that only 21.6% of adults with T2D achieved the recommended levels of PA - defined as at least 150 min of moderate-intensity aerobic physical activity throughout the week- and the average sitting time was > 12 h/ day [18]. Additionally, more than half of adult Omanis consume unhealthy diet leading to excess weight.

The multi-center Look AHEAD project has provided a high quality evidence about the effectiveness of lifestyle modification in diabetes management [19, 20]. The primary objective of this randomized controlled trial was to examine the long-term effects of lifestyle interventions- defined as 175 min of PA per week and a calorie counting with inclusion of fat gram counting and portion controlled- on cardiovascular morbidity and mortality in 5145 overweight or obese participants with diabetes. Despite the debatable lack of effectiveness of the intensive lifestyle intervention program on the cardiovascular morbidity and mortality, significant positive effects on weight, waist circumference, physical fitness and HbA1C were highly noted [21–23].

Current evidence on lifestyle including PA and dietary interventions in diabetes care comes mostly from Western countries, however results were diverse [24]. There was a variation in the type of interventions in terms of setting (clinical vs community), intervention methods (PA consultations, exercise sessions, or use of technology) and duration (short of 3–6 months vs long ≥12 months). Successful interventions have demonstrated that in obese patients with diabetes, PA and more extreme dietary energy restriction with very low-calorie diets can reduce HbA1c to < 6.5% and fasting glucose to < 126 mg/dL without pharmacological therapy or surgical procedures [25, 26].

Incorporating behavior change techniques (BCTs) in PA interventions has been shown to effectively move individuals from ‘inactive’ to ‘active’ stages of change for PA [27] and in weight management [28]. Whilst there is a large number of BCT’s, these have been standardised by Abraham and Michie [29] to assist the development of lifestyle interventions [30]. Avery et al. (2015), distinguished five context-appropriate BCTs for use during time-constrained consultations in diabetes care. These include “prompt focus on past success”, “barrier identification”, “use of follow-up prompts”, “providing information on where and when to perform the behaviour” and “prompt review of behavioural goals of PA” [27].

Consistent with the socio-ecological models of health behaviour (PA and SB) [31–33], and the Behavioural Change Wheel (BCW) model [30], the work presented in this proposal is a continuation of series of published studies to specifically promote healthy lifestyle in adults with diabetes primary care providers in Oman [18, 34–36]. Results showed that PA consultations linked to BCTs, devices to support walking such as pedometers, and use of phone applications were significantly associated with positive changes in PA behaviour including sitting time. The current proposal, in addition to PA, integrates dietary advice and includes innovative use of technology to enhance excess weight reduction and glycemic control in adults with diabetes. This proposal also integrates SB which is a growing research area that is under reported in Arabic speaking countries namely Oman. Results from this study is hoped to influence changes in the current national diabetes management policies and guidelines by providing evidence on effective lifestyle interventions using artificial intelligence within routine diabetes primary health care settings and highlighting the capacities needed to do so.

### Hypothesis

Other effective methods are needed to promote healthy lifestyle among Omani patients with T2D. We expect that a multi component intervention including phone consultations, use of pedometers and a smart phone application are effective in behavior change to promoting PA and healthy diet among patient with T2D in primary care compared with usual care.

### Primary objective

To evaluate the effectiveness of phone consultations and use of pedometers and a smart phone application in changing to positive behavior of PA and healthy diet and their impact on reducing excess weight [measuring body mass index (BMI)] and glycemic control (HbA1c).

### Secondary objectives

Estimate the impact on cardio-metabolic risk factors by measuring blood pressure and lipid profile at baseline and 12 months.

Estimate the impact on developing diabetes complications, by performing blood tests for kidney function, screen for retinopathy, diabetic foot exam findings at baseline and 12 months.

Estimate the impact of the intervention on change in PA and sitting time at 12 months follow up from baseline.

Estimate the impact of the intervention on the course of diabetes drugs/treatment plans at 12 months.

To examine the feasibility of the intervention (content, delivery and satisfaction) to the participants and care providers.

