## Methods

### Study setting

A one year 1:1 cluster randomised control trial in eight primary care facilities in A’Seeb Wilayat, which will be randomly allocated (using random numbers table generated in SPSS v21) to either the intervention components or usual care.

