#### Exclusion criteria

Patients with:
A history of myocardial infarction in the previous 6 monthsA serum creatinine > 140 mmol/L (from previous recorded readings in the electronic health information system)Diabetic foot ulcers or at high risk of ulcer (severe peripheral neuropathy)Repeated hypoglycaemia or severe hypoglycaemia in previous 12 monthsNo internet access for the phone applicationPhysical activity > 150 min per weekHbA1c ≤7%

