### Randomisation

The study is a 1 year 1:1 cluster randomized controlled trial of the lifestyle intervention versus usual care. A cluster randomisation design will be used to minimize between group contamination by having the two groups (intervention and comparison) from independent health centres. Group allocation will be generated using a random numbers table generated in SPSS v21done by an independent statistician at MOH. All health facilities (8) will be randomised to deliver either the intervention (*n* = 4) or usual care (n = 4). Health facilities will be informed of their allocation verbally by the project investigator and will receive an envelope containing invitation letter and project materials.

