### Sample size calculation

The study is powered to detect a change considered to be both meaningful and plausible on the primary outcome. A sample size of 392 (196 in each arm) will allow measuring a between group difference of 7% in BMI and 0.6%in HbA1c over 12 months from baseline, within a power of 80%, significance level of 5%, [19, 37] and a standardised difference of 0.394 (i.e. 0.394 of a standard deviation can be detected) under an Intra-cluster correlation coefficient of 0.01). With a drop-out rate of 20% and a recruitment rate of 70% the required sample size is 750 (375 in each arm). The equation below was used to calculate the sample size based on evidence from nearby countries, the UAE [38].

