### Statistical analysis

The analysis plan was adopted for a previous RCT on physical activity in diabetes in Oman [36]. Once all participants have been randomised, descriptive statistics including t-test for continuous variables and chi square for binary variables will be used to compare the two group’s variables at baseline. Descriptive analysis will also be used for summary statistics on patient assessment, eligibility, recruitment, withdrawal.

The primary outcome which is the rate of PA and healthy diet score, BMI and glycated hemoglobin over 12 months for all participants in both trial arms at 3, 6, and 12 months will be measured, summarized and tabulated for both study arms. Graphical illustration (box plots, histograms and bar charts) will be used where appropriate and the distributions of all outcome measures will be checked and transformed where appropriate. The main analysis will be linear regression modeling to test the main hypothesis related to the superiority of the proposed intervention in promoting healthy lifestyle compared with control group. All outcomes will be analysed adopting an intention-to-treat principle and all persons will be analysed in the groups to which they were randomised. We will try to minimize missing of data collected by ensuring complete and accurate data entry, however multiple imputation on the longitudinal data will be performed if we face missing data. For secondary analyses, logistic regression will be used adjusting for clustering of patients within health care facilitates.

Analysis and reporting of the results will follow the Consolidated Standards of Reporting Trials guidelines (CONSORT) for reporting RCTs [39]. SPSS version 21 will be used for data analysis.

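### The secondary objective on developing complications can give only an imprecise, exploratory estimate, and logistic regression of 12-month status would count disease already present at baseline

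*Protocol article*

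**What the plan says.** The article's Secondary objectives include (times in months) this one: "Estimate the impact on developing diabetes complications, by performing blood tests for kidney function, screen for retinopathy, diabetic foot exam findings at baseline and 12". The design is "A one year 1:1 cluster randomised control trial in eight primary care facilities", and under Randomisation "All health facilities (8) will be randomised to deliver either the intervention" or usual care, four facilities to each.

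The Sample size calculation rests on BMI and HbA1c: "A sample size of 392 (196 in each arm"), "within a power of 80%, significance level of 5"%, and "a standardised difference of 0.394", with an ICC of 0.01. This is then raised to 375 per arm for drop-out and recruitment rate. No complication incidence, event definition or power is given.

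The Statistical analysis section states one method at this level: "For secondary analyses, logistic regression will be used adjusting for clustering of patients within health care facilitates".

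The Exclusion criteria remove patients with raised serum creatinine and those with "Diabetic foot ulcers or at high risk of ulcer (severe peripheral neuropathy"). They do not remove retinopathy or milder kidney or foot disease. The section on physiological and medical history data lists renal and eye conditions among the comorbidities to be recorded.

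Table 2, introduced as describing all relevant outcomes, has no row for kidney function, retinopathy or foot findings.

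**The concern.** The objective is worded as an effect on new disease, but three things stand between that wording and a usable result.

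- **Precision.** One year and eight facilities give little information on yes/no events unless they are common.
- **Who is counted.** People with eye disease, or with kidney disease below the creatinine limit, can be enrolled. A logistic model of complication status at 12 months, fitted to everyone, would treat their existing disease as an outcome.
- **No endpoint.** The outcome table does not define these measures, so nothing in the article says what is to be modelled.

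At stake is how a wide interval gets read in a trial meant to inform national diabetes guidelines, and whether chance differences between facilities in baseline disease are mistaken for an effect or hide one.

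**Working it through.** **Reproducing the plan's figure.** Inputs from the Sample size calculation: 0.394 SD, 80% power, 5% significance (taken as two-sided), ICC 0.01. Without clustering, n per arm = 2 × ((1.960 + 0.842)/0.394)² = 101.1. The design effect is 1 + (m − 1) × ICC, with m patients per facility.

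- m = 375/4 = 93.75: design effect 1.9275, n = 194.9. This matches 196 closely.
- m = 196/4 = 49: design effect 1.48, n = 149.7. This does not match.

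So 196 is consistent with about 94 patients per facility. The article does not state m.

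**Analysed number.** Two readings are carried: 196 per arm, and 375 × 0.8 = 300 per arm if 375 are enrolled. If 375 are instead approached, 375 × 0.7 × 0.8 = 210 remain, close to the first reading.

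- 196 per arm: m = 49, design effect 1.48, effective n = 196/1.48 = 132.4
- 300 per arm: m = 75, design effect 1.74, effective n = 300/1.74 = 172.4

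**Power for a halving.** Assumptions not in the article: the control-arm 12-month risk p, and that the ICC of 0.01 also holds for complications. With q = p/2 and p̄ = (p + q)/2, power = Φ[(p − q − 1.96·s0)/s1], where s0 = √(2p̄(1 − p̄)/n_eff) and s1 = √((p(1 − p) + q(1 − q))/n_eff). At p = 0.05 and n_eff = 132.4, s0 = 0.02335 and s1 = 0.02330. The argument is (0.025 − 0.04576)/0.02330 = −0.89, and power is 0.19.

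The last column is the 95% interval for the risk ratio if the arms do not differ, exp(±1.96·√(2(1 − p)/(n_eff·p))).

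| Analysed per arm | Assumed risk | Control events | Power, halving | Interval at no difference |
|---|---|---|---|---|
| 196 | 2% | 3.9 | 10% | 0.19–5.4 |
| 196 | 5% | 9.8 | 19% | 0.35–2.9 |
| 196 | 10% | 19.6 | 34% | 0.49–2.1 |
| 196 | 20% | 39.2 | 63% | 0.62–1.6 |
| 300 | 2% | 6.0 | 12% | 0.23–4.4 |
| 300 | 5% | 15.0 | 23% | 0.40–2.5 |
| 300 | 10% | 30.0 | 42% | 0.53–1.9 |
| 300 | 20% | 60.0 | 74% | 0.66–1.5 |

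These figures are generous. They treat everyone as at risk, and they use a normal reference with only eight clusters. With a t reference on 6 degrees of freedom, the 196-per-arm powers fall to 8%, 15%, 26% and 49%. The approximation is rough at the lowest event counts.

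**Prevalent disease.** Let v be the share with the condition at entry, and suppose it persists. Status at 12 months is then v + (1 − v)p under control and v + (1 − v)p/2 after a halving. The difference shrinks by the factor (1 − v), the ratio moves towards 1, and any between-arm difference in v enters the comparison directly.

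**Kidney function as a continuous measure.** The detectable difference at 80% power is 2.802 × √(2/n_eff): 0.34 SD with 196 per arm and m = 49, and 0.30 SD with 300. On the article's own figures it is 0.394 SD. All are before baseline adjustment.

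**The case against.** The best defence is that this is one of five secondary objectives, that it says estimate and promises no test, and that the hypothesis, primary objective and conclusion claim nothing about complications. An unpowered secondary objective is ordinary. That stands: low power alone is not a defect here, and a reader who inferred that the objective cannot be answered, or that a null result is nearly certain, would go too far.

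Other strong readings are also unsupported:

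- **Only a few events per arm.** This depends on an incidence the article does not give. It holds at about 3% or below; at 10% there would be about 20 to 30 control events.
- **The exclusions remove the informative patients.** Leaving out people who already have a foot ulcer or raised creatinine fits a study of new complications. Only the high-ulcer-risk exclusion clearly lowers incidence, and retinopathy is untouched.
- **The large lifestyle trial in the Background shows this is hopeless.** Its debated result concerned cardiovascular morbidity and mortality, not kidney, eye or foot findings.

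It can also be said that the word developing, with examinations at both time points, implies restriction to people at risk, and that such detail may sit in an analysis plan not shown. The data for restriction are indeed planned. The logistic sentence may not be meant for every secondary outcome either, since Table 2 lists lipids and blood pressure as continuous. But it is the only secondary method stated, nothing limits it to participants free of the finding, and the table offers no definition that would settle the matter.

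**Conclusion.** The point holds as a matter of analysis and wording. For yes/no complications the trial can offer an imprecise, exploratory estimate: power for a halving is about 10–12% at 2% risk, 19–23% at 5% and 34–42% at 10%, and it stays below 80% even at 20%. At 2% or 5% the interval under no difference spans both a halving and a doubling. This rests on assumed incidences and on the ICC of 0.01 applying to complications; it does not depend on which analysed number is used.

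Separately, the stated logistic regression, if applied to 12-month status in all participants, would mix existing renal and eye disease with new disease. Kidney function is better placed, because a continuous comparison could detect roughly 0.34–0.39 SD on 196 per arm. That would be evidence on a marker, not on a developed complication.

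**What to change.** 1. Label the objective exploratory.
2. Report new retinopathy and new foot findings at 12 months by arm, among participants free of that finding at baseline, with counts and cluster-adjusted intervals.
3. Analyse the planned kidney function blood test as a continuous 12-month value adjusted for its baseline value and for clustering, and describe it as a marker.
4. Add the three measures to Table 2 with their time points and variable types, so that the table and the Secondary objectives agree.

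No extra tests or visits are needed, because the examinations at baseline and 12 months are already planned. The cost is a few lines of text, a smaller denominator for the eye and foot outcomes, and giving up a confirmatory claim on complications.

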## Methods

### Study setting

A one year 1:1 cluster randomised control trial in eight primary care facilities in A’Seeb Wilayat, which will be randomly allocated (using random numbers table generated in SPSS v21) to either the intervention components or usual care.

### Eligible criteria

#### Inclusion criteria

Adults aged18–65 years of ageDiagnosed with diabetes and overweight/ ObeseAttending (registered) health facilities for at least 6 monthsHbA1c > 7% (≥ 48 mmol/mol) according to Oman diabetes management guidelines.Assessed by project officer as having inactive behaviorNo contraindication to physical activityNot on a restricted diet.Able to speak and read ArabicWilling and able to provide written informed consent to the studyCan use phone applications

#### Exclusion criteria

Patients with:
A history of myocardial infarction in the previous 6 monthsA serum creatinine > 140 mmol/L (from previous recorded readings in the electronic health information system)Diabetic foot ulcers or at high risk of ulcer (severe peripheral neuropathy)Repeated hypoglycaemia or severe hypoglycaemia in previous 12 monthsNo internet access for the phone applicationPhysical activity > 150 min per weekHbA1c ≤7%

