**Secondary Outcomes**			
**Socio-demographic data**	**Questionnaire**	**B**	**Binary / numerical**
**Height (m)**	**Stadiometer**	**B**	**continuous**
**Pedometer**	**Reporting step counts**	**B, 3F, 6F, 12F**	**numerical**
**GPAQ-MET-mins/week**	**Questionnaire**	**B, 3F, 6F, 12F**	**continuous**
**Diet assessment tool**	**Questionnaire**	**B, 3F, 6F, 12F**	**continuous**
**Lipid profile (mmol/l)**	**Blood test (venous fasted sample)**	**B, 3F, 6F, 12F**	**continuous**
**Blood pressure (mmHg)**	**Sphygmomanometer**	**B, 3F, 6F, 12F**	**continuous**
**Exit survey**	**Questionnaire (participants and project officers)**	**12F**	**description**

(B = baseline; 3F = 3 month follow-up; 6F = 6 month follow up; 12F = 12 month follow-up)

^a^while blood collection for HbA1c at 12 month is mandatory, it is only done at baseline, 3 and 6 month if missing from the electronic health information system or recorded within more than 4 months prior to the measurement visits

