#### Physiological (medical history) data

This will include duration of diabetes, BMI, blood pressure, lipid profile, and presence of any comorbidities defined as cardiovascular, hyperlipidemia, thyroid abnormalities, renal, eye, musculoskeletal, or any other recorded condition in the electronic health information system coinciding with diabetes. Drug (treatment) history: type and dose will also be recorded.

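### The only kidney-specific exclusion is set at serum creatinine above 140 mmol/L, a level no patient can have, so as written it excludes no one

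*Protocol article*

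**What the plan says.** The Exclusion criteria list one criterion on kidney function: "serum creatinine > 140 mmol/L (from previous recorded readings in the electronic health information system". The number and its unit appear nowhere else in the article.

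Kidney disease comes up in two other places, and neither is an eligibility rule:

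- Under Secondary objectives, the trial will estimate the effect on diabetes complications "by performing blood tests for kidney function, screen for retinopathy, diabetic foot exam findings at baseline and 12 months". Here kidney function is an outcome.
- Under Physiological (medical history) data, the investigators will record "presence of any comorbidities defined as cardiovascular, hyperlipidemia, thyroid abnormalities, renal, eye, musculoskeletal" and other conditions. Here renal disease is a baseline characteristic.

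The Inclusion criteria contain two general conditions: physical activity must not be contraindicated, and the patient must not be following a restricted diet. Neither mentions the kidney.

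**The concern.** An exclusion threshold works only if some patients can exceed it. A serum creatinine of 140 mmol/L is not a possible laboratory result, so nobody can meet this criterion as printed. The error sits in an operative eligibility rule that project officers are meant to apply at screening, not in background text. Since no other criterion deals with the kidney, literal use would leave the trial without a kidney-specific exclusion. Patients whom the sponsor presumably meant to keep out could then be enrolled. They would also enter the 12-month comparison of kidney function named in the Secondary objectives.

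**Working it through.** The check is a unit conversion. The plan has no derived figure to reproduce here, because the threshold is simply stated.

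**Inputs**

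- Threshold: 140 mmol/L (Protocol article, Exclusion criteria).
- Molar mass of creatinine: about 113.12 g/mol, a physical constant that is not in the documents.
- Range of human serum creatinine, from normal to extreme renal failure: 0.05 to 3 mmol/L. This is an assumption; the documents give no range.

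**Step 1. Convert the threshold.**

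- Mass per litre: 140 mmol/L × 113.12 mg/mmol = 15,837 mg/L, or about 15.8 g/L.
- Per decilitre: 15,837 ÷ 10 = about 1,584 mg/dL.
- In micromoles: 140 × 1,000 = 140,000 µmol/L.

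**Step 2. Compare with the assumed human range.**

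| Serum creatinine (mmol/L) | Threshold ÷ value |
|---|---|
| 0.05 | 2,800 |
| 0.1 | 1,400 |
| 0.5 | 280 |
| 1.0 | 140 |
| 2.0 | 70 |
| 3.0 | 46.7 |

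Every ratio is far above 1, so no value in the range exceeds the threshold and the share excluded as written is 0%. The conclusion does not depend on the upper limit chosen: that limit would have to be about 47 times higher before any patient reached the threshold.

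**Step 3. Ask in which usual unit the number 140 is a possible result.**

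- As mmol/L: 140 against an upper limit of 3. Not possible.
- As mg/dL: 140 × 10 ÷ 113.12 = about 12.4 mmol/L, also above 3. Not possible.
- As µmol/L: 140 ÷ 1,000 = 0.14 mmol/L, inside the range.

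The number is possible in only one of the three usual units, which is why the text reads as a slip in the unit. This does not show what the sponsor intended; the number itself could also be wrong.

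**Step 4. Look for another rule that does the same work.** There is none. The two general inclusion conditions might remove some patients with severe kidney disease, but not through this criterion. The two other mentions of the kidney concern an outcome and a recorded comorbidity.

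**The case against.** The strongest reply is that the slip reveals itself. Screening is done by project officers drawn from existing doctors, nurses, dieticians and health educators, and Recruitment of project officers says that they will be trained in screening. They will read values already held in the electronic record, in that system's own unit, and may well compare 140 with what they see there. This stands as a limit on the practical harm. It does not rescue the text, because the criterion then works only if staff silently override what is printed.

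It is also possible that a µ was lost when the published file was converted to text. That looks unlikely, since other special characters (≥ and ≤) survive in the same lists, but the typeset article settles it.

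A reader might infer four stronger things that the documents do not support.

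- **A count of wrongly enrolled patients.** This would need the share of screened patients above the intended level, which the article does not give. It would also require every officer to apply the impossible unit literally and no other criterion to remove anyone. Multiplying an assumed share by the 392 in the Sample size calculation would also put a screening proportion on a figure stated before the allowances for drop-out and recruitment rate.
- **Facilities guessing differently, so that clusters or arms diverge.** Different guesses need rival plausible units. Step 3 leaves only one, and nothing in the article ties such differences to arm.
- **A threshold 1,000 times any possible result.** The factor of 1,000 is the ratio of mmol to µmol. Against extreme values the factor is about 47.
- **An error in the age of the reading.** The phrase "from previous recorded readings in the electronic health information system" sets no time limit, whereas neighbouring criteria use 6 and 12 months. How old a reading may be is detail that a condensed article can leave to the full protocol. The HbA1c rule in the footnote to Table 2 ("recorded within more than 4 months prior to the measurement visits") governs reuse of values at measurement visits, not eligibility, so nothing is contradicted. Nor does the article oblige the sponsor to base eligibility on the baseline kidney test, which the Secondary objectives mention but Table 2 does not list.

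Finally, the article gives no reason for the criterion, so calling it a safety rule is an inference.

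**Conclusion.** The point holds in a narrow form. The only kidney-specific exclusion is stated in a unit that makes it impossible to meet, and nothing else in the article corrects it. Applied literally, it excludes 0% of patients. This rests on the molar mass of creatinine and on human values staying well below 140 mmol/L, which the assumed upper limit of 3 mmol/L satisfies with a margin of about 47.

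How many patients would be affected in practice is unknown, and may be few or none if staff recognise the slip. Sample size, power and the primary outcomes are not shown to be affected. The correction is still needed because this is a live decision rule that is wrong as written.

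**What to change.** The sponsor should confirm the intended number and unit and correct the criterion in the Exclusion criteria before it is used for screening. Any screening form or training material that repeats the criterion should be brought into line.

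The cost is a one-line correction, with no new test and no change to the design, sample size or analysis. The choice of threshold, the age of the reading and any link to a baseline test remain with the sponsor; none is proposed here.
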